**Fig. 3 Fig3:**
[figure not shown]
CONSORT flow diagram

### Statistics

Descriptive statistics will be utilized to check for exchangeability between the two groups according to baseline variables. Categorical variables will be analyzed with a Chi-square or Fischer’s exact test depending on Cochran’s rule. Continuous and discrete variables will be analyzed with an unpaired t-test or Wilcoxon rank-sum test depending on the distribution of the variables. The primary, secondary and exploratory endpoints will also be compared using descriptive statistics. For continuous and discrete variables, repeated measurement ANOVA or Kruskal–Wallis rank-sum tests will be used to compare these variables across timepoints stratified according to the operation method. The normality and heterogeneity of variance assumptions for the t-test and the ANOVA will be graphically assessed using quantile–quantile plots. A mixed-effect model will be utilized to analyze the degree of systemic and peritoneal inflammatory response because of repeated measurements. Logistic regression will be utilized to analyze perioperative complications, 30-day mortality, surgical and medical complications. Odds ratios with 95% confidence intervals will be reported. A poisson or linear regression will be used for time from treatment start until end, and the Quality of Recovery questionnaire (QoR-15 score). Quantile–quantile plots will be used to check if the deviance and the Pearson residuals are normally distributed, and a scatterplot of the deviance and Pearson residuals will check the closeness of the model to our data. If the residuals for the mixed-effect model are not normally distributed, a log transformation of the outcome may be necessary. If the residuals are still not normal distributed, a mixed-effect gamma model will be performed. If these residuals are not normally distributed, logistic regression with another type of link function will be utilized. If deviance residuals are not normally distributed and are not close to zero for the poisson regression, a negative binomial regression or linear regression with bootstrapped confidence intervals will be utilized. If adjustments in the mixed-effect model are necessary, a univariate analysis with only the exposure variable will be included as a sensitivity analysis. If the negative binomial regression is utilized, a poisson regression will be added as a supplementary analysis. No subgroups analysis will be a part of this project. All regression analyses will follow the one-in-ten rule to avoid overfitting. No interim analyses will be performed as no similar prospective randomized clinical trial has previously been performed, so completion of this study is of great importance.

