### Outcomes

**Primary endpoint**:Levels of systemic inflammatory response expressed by serum C-reactive protein (CRP) and interleukin 6 (IL-6) measured postoperatively day one to day three**Secondary endpoints** Levels of systemic inflammation in serum expressed by: Eotaxin, Eotaxin-3, granulocyte–macrophage colony-stimulating factor (GM-CSF), interferon-gamma (IFN-γ), interleukin 1 alpha (IL-1α), interleukin 1 beta (IL-1β), interleukin 2 (IL-2), interleukin 4 (IL-4), interleukin 5 (IL-5), interleukin 7 (IL-7), interleukin 8 (IL-8), interleukin 10 (IL-10), interleukin 12 (IL-12), interleukin 23 (IL-23), interleukin 13 (IL-13), interleukin 15 (IL-15), interleukin 16 (IL-16), interleukin 17a (IL-17A), interferon gamma-induced protein 10 (IP-10), monocyte chemoattractant protein 1 (MCP-1), monocyte chemoattractant protein 4 (MCP-4), macrophage derived chemokine (MDC), macrophage inflammatory protein 1 alpha (MIP-1α), macrophage inflammatory protein 1 beta (MIP-1β), thymus and activation regulated chemokine (TARC), tumor necrosis factor alpha (TNF-α), tumor necrosis factor alpha (TNF-β) lymphotoxin alpha (LT-α), vascular endothelial growth factor A (VEGF-A) and interleukin 1 receptor antagonist (IL-1RA) measured on the first three postoperative days.Postoperative surgical and medical complications (30 days) according to Clavien-Dindo classification [27] and Comprehensive Complication Index [28].Postoperative dynamic pain registration (visual analog scale (VAS)) at rest twice daily (morning and evening) and registration of opioid consumption in medical charts.Intraoperative blood loss (mL).Conversion rate to open surgery.Total surgical duration (minutes).Total anaesthesia duration (minutes).Lymph node yield.Length of hospital stay (hours/days).Time to passage of flatus (hours).Time to passage of stool (hours/days).

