### Participant timeline, data collection and follow-up

The preoperative assessment will consist of information concerning baseline data (age, gender, body-mass index (BMI), ASA-score, Charlson Comorbidity Index (CCI), WHO performance status, date of diagnosis, type of planned operation, date of randomization and operation (Figs. 1 and 2). Patients will be preoperatively asked to fill out the QoR-15 questionnaire at baseline and from the first until the third postoperative day [29]. A full recovery status (QoR-15) will be collected 14 days postoperatively.

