### Sample size

The Monte Carlo method calculated the power of the mixed effect model used for the log-normal distributed outcome of C-reactive protein (CRP) levels. The sample size calculation was based on the primary outcome (the systemic inflammatory postoperative response expressed by pro-inflammatory and anti-inflammatory cytokines). It was assumed that the CRP level in the group of patients undergoing laparoscopic surgery for colorectal cancer would be 19% higher than patients with robot-assisted surgery, with an interpersonal variation of 0.63 and an intrapersonal variation of 0.34 for the logarithmic transformed CRP. The mixed-effect model was adjusted for type of operation and time. The assumption of CRP among elective malignant colonic resections was based on postoperative measurements on days 1–3 from an observational data set of 298 patients undergoing surgery for colorectal cancer using robot-assisted or laparoscopic methods from 2017 to 2019 at our surgical department, Hospital Sønderjylland, University Hospital of Southern Denmark  [17]. To obtain a power of 86% and an alpha level of 0.05 for a two-sided p-value, we aimed to include a minimum of 42 patients.

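### The rank option for comparisons over time within each arm, Kruskal–Wallis, assumes independent groups, but the timepoints are the same patients; a paired rank test is needed (minor)

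*Protocol article*

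**What the plan says.** In the Statistics section, continuous and discrete variables are first assigned an unpaired t-test or a Wilcoxon rank-sum test. For change over time the section then says that "repeated measurement ANOVA or Kruskal–Wallis rank-sum tests will be used to compare these variables across timepoints stratified according to the operation method". Read as written, the groups being compared are the timepoints, and the comparison is made separately within the robot-assisted and the laparoscopic arm.

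The timepoints are visits of the same patients. The primary endpoint in the Outcomes section is "serum C-reactive protein (CRP) and interleukin 6 (IL-6) measured postoperatively day one to day three". The section on participant timeline has patients "fill out the QoR-15 questionnaire at baseline and from the first until the third postoperative day", with a further QoR-15 assessment 14 days after surgery.

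The Statistics section recognises the repeated structure elsewhere: "A mixed-effect model will be utilized to analyze the degree of systemic and peritoneal inflammatory response because of repeated measurements". The Sample size section gives the size of the dependence for CRP: "an interpersonal variation of 0.63 and an intrapersonal variation of 0.34 for the logarithmic transformed CRP".

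**The concern.** Repeated-measures ANOVA and Kruskal–Wallis are offered as parametric and rank counterparts, but they are not. The first removes differences between patients before it tests for change over time. The second treats each day as a fresh, independent sample. The rank counterpart of a one-way repeated-measures ANOVA is Friedman's test.

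When days are strongly correlated, Kruskal–Wallis judges the day-to-day differences against the full spread between patients. It then almost never rejects. The rank route may well be taken, since the protocol itself treats CRP as log-normal and the choice depends on normality plots. What is at stake is the description of how markers and recovery scores change over time within an arm: p-values from the rank option would be invalid, and real changes would often be missed.

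**Working it through.** The plan states no operating figure for this test, so there is none to reproduce. Its 86% power relates to the mixed-effect model for CRP and is not used here.

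**Inputs from the protocol article**
- Between-patient variation 0.63 and within-patient variation 0.34 for log CRP (Sample size). The text does not say whether these are standard deviations or variances, so both readings are carried.
- 25 patients per arm (Recruitment, randomization and blinding).
- Three postoperative days (Outcomes).

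**Step 1: correlation between days within a patient**

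Correlation = between-patient variance / (between-patient variance + within-patient variance).
- Standard-deviation reading: 0.63² / (0.63² + 0.34²) = 0.3969 / (0.3969 + 0.1156) = 0.3969 / 0.5125 = 0.77.
- Variance reading: 0.63 / (0.63 + 0.34) = 0.63 / 0.97 = 0.65.

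Only the remaining share of the variance, 1 − 0.77 = 0.23 or 1 − 0.65 = 0.35, contributes noise to a comparison between days. Kruskal–Wallis uses all of it as the yardstick.

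**Step 2: rejection rate with no change over time**

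One arm was simulated as a normal patient effect plus a normal residual on each of three days. It was tested across days at 0.05, with 10,000 runs per reading.

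| Reading (n = 25) | Kruskal–Wallis | Friedman | Repeated-measures ANOVA |
|---|---|---|---|
| Standard deviations | 0.01% | 5.2% | 5.1% |
| Variances | 0.07% | 5.2% | 4.9% |

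With 21 patients per arm (half of the protocol's minimum of 42), Kruskal–Wallis gives 0.03% and 0.14%. The nominal rate is 5%.

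**Step 3: rejection rate with a change over time**

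Assumption, not from the documents: log CRP rises by 0.15 per day (0, 0.15, 0.30).

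| Reading (n = 25) | Kruskal–Wallis | Friedman | Repeated-measures ANOVA |
|---|---|---|---|
| Standard deviations | 5% | 64% | 79% |
| Variances | 2% to 3% | 24% to 26% | 33% |

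The ranges cover separate simulation runs. A different assumed pattern (0, 0.3, 0.15) on the standard-deviation reading gives 4%, 63% and 78%, so the ordering does not depend on the particular shape.

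**Step 4: what the within-arm test can show about the arms**

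Adding a constant log(1.19) = 0.174 to every value in an arm, the size of the difference assumed in the Sample size section, leaves the ranks within that arm unchanged. In one simulated arm the Kruskal–Wallis p-value was 0.831 before and after. A test across days within an arm therefore does not respond to a constant difference between the arms.

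**The case against.** Much can be said in the plan's defence.

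- The option named first, repeated-measures ANOVA, respects the pairing. This stands: the fault lies in the rank option alone, and nothing requires the ANOVA to be removed.
- The arms are compared elsewhere, by t or Wilcoxon tests, the mixed-effect model for inflammation, and regressions for other outcomes. This stands. A reader might infer that the trial lacks a valid comparison of robot-assisted with laparoscopic surgery, or that its primary result depends on Kruskal–Wallis. The document supports neither.
- The error is conservative. This stands: it does not create false claims of change over time, and a reader should not infer inflated type I error.
- The sentence might mean a comparison of the two operation methods at each timepoint. With two groups Kruskal–Wallis amounts to the Wilcoxon rank-sum test and would be valid. The wording does not favour this, because it makes timepoints the compared groups and operation method the stratum, and the Wilcoxon test is already named for the arms.

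A further temptation is to predict that a significant result in one arm and a non-significant one in the other will be reported as an effect of the robot. With equal true change and 50% power in each arm, the arms would disagree in 2 × 0.5 × 0.5 = 50% of trials. That power is an assumption with no link to this protocol. At the 5% power found above for Kruskal–Wallis the figure would be 2 × 0.05 × 0.95 = 9.5%. No section says that conclusions about the arms will be drawn this way, so this is a reason for a clarifying sentence and not a defect in itself.

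**Conclusion.** The rank option is wrong as written, and the weight of the point is minor. On the protocol's own figures for log CRP, the test rejects in roughly 0% to 0.1% of null cases instead of 5%, whichever way the variation figures are read. This rests on normally distributed patient effects and residuals, and on equal correlation between all days. The loss of power also rests on an assumed time pattern, so the 5% versus 64% contrast illustrates the problem and does not forecast this trial's result.

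The calculation uses CRP because it is the only endpoint with published variation figures. For CRP, IL-6 and the other cytokines the mixed-effect model carries the inference. The choice of rank test has more bearing on repeated outcomes outside the inflammatory panel, such as pain scores and QoR-15, for which the Statistics section does not name the mixed model. Their correlation between days is not given, so no size can be stated for them.

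**What to change.** In the Statistics section, replace Kruskal–Wallis with Friedman's test, or another paired rank method, wherever a variable is compared across timepoints within an operation method. Repeated-measures ANOVA can stay as the parametric option.

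Add one sentence: these within-arm tests are descriptive, and conclusions about the systemic and peritoneal inflammatory response in the two arms come from the mixed-effect model, through the arm and arm-by-day terms with 95% confidence intervals, not from setting within-arm p-values side by side.

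It would also help to state whether 0.63 and 0.34 are standard deviations or variances.

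The cost is a change of wording. The design, sample size and data collection are unaffected.

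### Poisson regression is allowed for a duration and for QoR-15 without a dispersion safeguard, and the rule for leaving it can keep a model whose standard errors are too small

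*Protocol article*

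**What the plan says.** All on this point is in the protocol article.

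- **Model** (Statistics): "A poisson or linear regression will be used for time from treatment start until end, and the Quality of Recovery questionnaire (QoR-15 score"). No criterion is given for choosing one or the other.
- **Checks** (Statistics): "Quantile–quantile plots will be used to check if the deviance and the Pearson residuals are normally distributed". A plot of the same residuals is also meant to show how well the model fits. The second check has no threshold.
- **Exit rule** (Statistics): "If deviance residuals are not normally distributed and are not close to zero for the poisson regression". In that case the analysis moves to a negative binomial model, or to a linear model with bootstrapped intervals. If the negative binomial model is used, the Poisson fit is still reported as a supplementary analysis.
- **Units** (Outcomes): surgical duration is in minutes. Hospital stay is listed as "Length of hospital stay (hours/days"), and time to stool is likewise left open between hours and days.
- **QoR-15** is an exploratory endpoint. Its schedule (Participant timeline) reads "Patients will be preoperatively asked to fill out the QoR-15 questionnaire at baseline and from the first until the third postoperative day", with a further assessment on day 14.
- **Size** (Recruitment, randomization and blinding): 50 patients, 25 per arm.

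**The concern.** A Poisson model fixes the variance at the mean. That can be defended for counts of events. It has no basis for elapsed minutes or a summed questionnaire score, whose variance is a separate quantity. Without a dispersion estimate or robust variance, the model's standard error takes no account of how much patients actually differ.

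The exit rule should catch this but is built on the wrong feature. A Q-Q plot read for normality judges the shape of the residuals, whereas overdispersion is a matter of their scale. The rule also joins its two conditions with 'and'. Residuals that are far too large but roughly normal meet only one condition, and the analyst following the text stays with Poisson.

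At stake are false positive claims on operating time (secondary) and recovery (exploratory). A further problem is that two models with very different standard errors can be chosen between after the data are seen.

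**Working it through.** The document gives no figure for these outcomes, so there is none to reproduce. The 25 per arm comes from the article. The 5% two-sided level is stated there only for CRP and is carried over here. All means and SDs are assumptions.

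**1. Standard errors.** For two arms of size n with common mean m and standard deviation s:

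- Poisson SE of the log ratio = sqrt(2/(n·m))
- actual SE ≈ (s/m)·sqrt(2/n)
- ratio k = actual/Poisson = s/sqrt(m)
- true type I error at nominal 5% ≈ 2·(1 − Φ(1.96/k))

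Example, mean 180 min and SD 45: Poisson SE = sqrt(2/(25·180)) = 0.0211; actual SE = 0.25·sqrt(2/25) = 0.0707; k = 45/sqrt(180) = 3.35; 1.96/3.35 = 0.584; type I error = 56%.

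**2. Results.** The simulations used 20,000 null trials, with lognormal durations and normal QoR-15.

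| Outcome (assumed) | k, formula | Type I, formula | Type I, simulated |
|---|---|---|---|
| Minutes, 180 / SD 20 | 1.49 | 19% | 19% |
| Minutes, 180 / SD 45 | 3.35 | 56% | 56% |
| Minutes, 200 / SD 60 | 4.24 | 64% | 65% |
| QoR-15, 110 / SD 10 | 0.95 | 4% | 4% |
| QoR-15, 110 / SD 15 | 1.43 | 17% | 17% |
| QoR-15, 110 / SD 20 | 1.91 | 30% | 30% |
| QoR-15, 110 / SD 25 | 2.38 | 41% | 39% |

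**3. Does the exit rule respond?** A Shapiro test on the deviance residuals stood in for the Q-Q plot. In the three surgical-duration scenarios it rejected normality in 8%, 21% and 26% of null trials, so 74% to 92% passed. The residual SD averaged 1.45, 3.21 and 4.02, where a well-fitting Poisson model gives about 1. In a separate run of 6,000 trials per scenario, the type I error among trials that passed was 18%, 56% and 65%. Passing the check therefore gives no protection. The closeness check was not simulated, because it has no threshold. Under the 'and', it cannot trigger a switch once normality has passed.

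**4. Units, if Poisson were also used for outcomes listed in hours or days.** Multiplying the time unit by c multiplies variance/mean by c, so k changes by sqrt(c). Between days and hours that is sqrt(24) = 4.9. Simulated hospital stay, rounded to whole units:

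- 4 days, SD 2.5: type I error 12% in days, 74% in hours
- 3 days, SD 1.5: 2.5% in days, 63% in hours

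**5. With a repair.** A robust variance gave 4.7% to 5.9% in every scenario and unit. The article's own negative binomial fallback gave 5.6% to 8.2% (500 runs each).

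**The case against.** The strongest reply is that Poisson is only one of two named options. Linear regression stands in the same sentence and its inference does not depend on the unit. A closeness check exists beside the Q-Q plot, and the fallback models largely repair the error once reached. All of this is correct. It does not remove the defect: nothing says when linear regression is to be preferred, and the exit rule need not reach the fallback.

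Several stronger readings are tempting but not supported:

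- *Baseline QoR-15 goes unused, or days are pooled as independent.* The article does not say which QoR-15 assessments enter the regression or with what covariates. It also plans repeated-measures ANOVA across timepoints, which could include baseline. Such detail is commonly left to the full protocol or SAP.
- *The planned checks cannot detect the problem.* Too strong. For skewed hospital stays in hours, the normality test rejected in 58% to 72% of runs. The checks are unreliable rather than blind.
- *The intervals are always far too narrow.* Not so. In days they may be slightly narrow or too wide, and at an assumed QoR-15 SD of 10 they are about right.
- *Unit dependence is established for hospital stay.* The Poisson sentence most naturally means surgical duration, which is fixed in minutes. Applying it to stay or time to stool is an assumption.

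**Conclusion.** The point holds in a limited form. As written, the plan permits a model that does not suit a duration or a questionnaire score. Following its stated exit rule can leave that model in place with badly understated standard errors.

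The type I error would be about 19% to 65% for surgical duration in minutes and about 4% to 41% for QoR-15, instead of 5%. These figures rest on the assumed means and SDs, on Poisson being chosen over linear regression, and on the fallback not being used. The square-root dependence on the time unit is algebra and needs no assumed values, but it matters only if Poisson is extended to outcomes left in hours or days.

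The consequence is confined to secondary and exploratory endpoints. The primary endpoint, analysed by a mixed-effect model, is untouched.

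**What to change.** - Name one primary method for these outcomes in advance: linear regression, on log time for durations, with robust or bootstrapped confidence intervals; or the Wilcoxon rank-sum test the plan already contains.
- If Poisson is kept, require a robust variance in every case and delete the trigger based on residuals being non-normal and not close to zero. The supplementary Poisson analysis should carry the same robust variance.
- State which durations the regression sentence covers, and fix one time unit per outcome.

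The cost is a change of analysis wording and wider intervals on secondary and exploratory endpoints. Log time changes the reported effect to a ratio of geometric means, and the Wilcoxon test gives no effect estimate by itself. No change to sample size, data collection or the primary analysis is needed.

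### The plan allows an unscaled Poisson regression for durations in minutes and for QoR-15, with no rule for choosing it and a fallback that can leave an over-dispersed fit in place

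*Protocol article*

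**What the plan says.** The Statistics section of the protocol article pairs two models for two kinds of outcome: "A poisson or linear regression will be used for time from treatment start until end", and, in the same sentence, for the QoR-15 score. It gives no criterion for choosing between them. Earlier in the section, a t-test or rank-sum test is also named for continuous variables in general.

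The Poisson fit is examined with quantile–quantile plots and with a further plot: "a scatterplot of the deviance and Pearson residuals will check the closeness of the model to our data". The condition for leaving it is "If deviance residuals are not normally distributed and are not close to zero for the poisson regression", after which "a negative binomial regression or linear regression with bootstrapped confidence intervals will be utilized". Even then Poisson is not dropped: "If the negative binomial regression is utilized, a poisson regression will be added as a supplementary analysis". The section mentions no dispersion parameter and no scaled or robust standard error.

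The Outcomes section records "Total surgical duration (minutes"), with anaesthesia duration in the same unit. For hospital stay it leaves two units open: "Length of hospital stay (hours/days"). Time to stool is treated likewise. These are secondary endpoints; QoR-15 is exploratory.

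**The concern.** A duration is a continuous measurement and QoR-15 is a questionnaire score. Poisson regression takes its standard error from the mean alone. If the true variance is φ times the mean, the reported standard error is too small by a factor √φ. Because φ changes with the unit, so does the p-value. Both problems disappear once the variance is estimated from the data.

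The fallback does not look for this directly. The sign of over-dispersion is large residuals, whatever their shape. Here large residuals cause a switch only when the residuals are also non-normal. A roughly symmetric operating time with a wide spread gives large, normal-looking residuals, and the rule keeps the fit.

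At stake is a claim that one technique has a shorter operating or anaesthesia time, or gives better early recovery scores, resting on an interval that is far too narrow.

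**Working it through.** **Inputs.** From the document: 25 per arm, and surgical and anaesthesia duration in minutes. The two-sided 0.05 level is taken from the sample size section. The document states no mean, SD or error rate for any duration or for QoR-15, so there is no figure of the plan's own to reproduce here; its only power figure concerns CRP. Means and SDs below are assumptions, shown as ranges.

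**Step 1: size of an unscaled Poisson Wald test.** With no true difference, its statistic has SD √φ instead of 1, where φ = SD²/mean. The type I error is therefore 2 × (1 − Φ(1.96/√φ)).

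| Assumed outcome | Mean | SD | φ | Type I error |
|---|---|---|---|---|
| Operating time, min | 180 | 30 | 900/180 = 5 | 38% |
| Operating time, min | 180 | 45 | 2025/180 = 11.25 | 56% |
| Operating time, min | 180 | 60 | 3600/180 = 20 | 66% |
| QoR-15 | 120 | 15 | 225/120 = 1.9 | 15% |
| QoR-15 | 110 | 15 | 225/110 = 2.0 | 17% |
| QoR-15 | 120 | 25 | 625/120 = 5.2 | 39% |
| QoR-15 | 110 | 25 | 625/110 = 5.7 | 41% |

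Simulation agrees: 37–67% for operating time and about 16–39% for QoR-15. At a mean of 180 min, Poisson is correct only if the SD is about √180 = 13 min. That is narrow for a trial that pools right-sided, left-sided and sigmoid resections.

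**Step 2: apply the fallback.** I simulated 4,000 null trials per scenario, with normal and log-normal durations. Shapiro–Wilk at 0.05 on the deviance residuals stood in for the quantile–quantile plot, and a t-test stood in for the linear fallback. The second condition was taken as always met, which favours the plan: residuals here have an SD of about √φ (2.2 to 4.5), not 1. For roughly normal operating times the residuals look normal in about 80–94% of trials, so Poisson is usually kept. Overall type I error falls only to 34–56%.

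**Step 3: models that estimate the variance.** On the same kind of data, linear regression or the t-test gives 3.6–5.5% and Pearson-scaled Poisson 4.5–6.1%. Negative binomial gives about 3–7%, with some fits failing to converge.

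**Step 4: unit dependence, if the model were also used for hospital stay.** Take 4.5 v 4.0 days, 25 per arm, so totals of 112.5 and 100 days.

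- In days: SE of the log ratio = √(1/112.5 + 1/100) = 0.137; z = ln(4.5/4.0)/0.137 = 0.86; p = 0.39.
- In hours: z is multiplied by √24 = 4.90, giving 4.20; p = 0.00003.
- t-test with assumed SD 2 days: p = 0.38 in either unit.

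With an assumed mean of 96 h and CV 0.4–0.6 (log-normal), plain Poisson in hours gives 62–74%. Stay is skewed, so the residuals look normal in only 58%, 43% and 30% of trials at CV 0.4, 0.5 and 0.6. With the fallback the error is about 24–38%. In days, φ is 0.64 to 1.44 and plain Poisson gives 1–10%.

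**The case against.** Four counter-arguments have weight.

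*Poisson is not imposed.* A reader might infer that the plan prescribes it for durations. The text offers linear regression in the same clause and t-test or rank-sum alternatives in the same section, and linear regression holds the 5% level. This stands. The defect is an open choice that includes one unsound option, so the error rates apply only if Poisson is chosen.

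*The diagnostics do consider residual size.* Closeness to zero is part of the trigger, and a scatterplot examines fit. It would be wrong to say that only shape is checked. But as written the size condition cannot act alone, and it has no threshold.

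*Hospital stay is not clearly covered.* A reader might infer that false positives for stay reach 62–74%. The Poisson sentence fits operating and anaesthesia time best, and nothing ties it to stay, flatus or stool. Those rates also ignore the fallback, which fires often on skewed data. The endpoints that the sentence most plainly covers have one fixed unit, minutes, so the team has no choice of unit to exploit there. All this stands, and the stay figures are conditional.

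*A supplementary Poisson fit is harmless.* Shown beside a negative binomial model it would not drive the conclusion. That is largely fair, but its interval would still be misleadingly narrow.

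**Conclusion.** The point holds in limited form. For durations in minutes and for QoR-15, the plan permits a model whose standard errors ignore the observed spread, gives no rule for choosing it, and may keep it when it fits badly. This is a stated rule that can give a wrong result, not detail left to an analysis plan.

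If Poisson is chosen, type I error for operating time is about 37–67% before the fallback and 34–56% after it. This rests on the assumed mean of 180 min, SD 30–60 and 25 per arm, and on the stand-ins for visual plots. For QoR-15, at the assumed values, it is about 16–39% before any fallback. If hospital stay were analysed the same way in hours, the error would be about 24–38% with the fallback, and the result would depend on the unit.

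These are conditional rates, not the expected false-positive rate of the trial. The primary CRP and IL-6 analysis uses a mixed model and is not affected. The point should be fixed; it concerns secondary and exploratory endpoints only.

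**What to change.** - Remove unscaled Poisson regression for durations and QoR-15, both as main and as supplementary analysis.
- Name one model per endpoint. For durations, use linear regression on log time and report the ratio of geometric means with a 95% CI, which does not depend on the unit. For QoR-15, use linear regression.
- If a Poisson model is kept, use quasi-Poisson or robust standard errors. Judge dispersion by Pearson chi-square divided by its degrees of freedom, and drop the joint normality-and-closeness trigger.
- State which endpoints the duration sentence covers, and fix one unit for each, including hospital stay and time to stool.

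The cost is a few sentences in the Statistics and Outcomes sections and no new data. Confidence intervals will be wider than under unscaled Poisson, because they will reflect the actual variability.

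### The residual-normality check is not limited to models it suits: it is invalid for the binary endpoints, and the sentence offering logistic regression with another link is unsound on either reading

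*Protocol article*

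**What the plan says.** All the relevant text is in the Statistics section of the protocol article, in this order.

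1. Binary outcomes: "Logistic regression will be utilized to analyze perioperative complications, 30-day mortality, surgical and medical complications". The effect measure is fixed without condition: "Odds ratios with 95% confidence intervals will be reported".
2. Other outcomes: "A poisson or linear regression will be used for time from treatment start until end", and also for the QoR-15 score.
3. Model check, directly after these: "Quantile–quantile plots will be used to check if the deviance and the Pearson residuals are normally distributed". A scatterplot of the same residuals is to show how close the model is to the data.
4. Fallbacks for the mixed-effect model: a log transformation first, then "If the residuals are still not normal distributed, a mixed-effect gamma model will be performed".
5. The next sentence: "If these residuals are not normally distributed, logistic regression with another type of link function will be utilized".
6. A separate rule for counts, which opens "If deviance residuals are not normally distributed and are not close to zero for the poisson regression" and leads to negative binomial regression or to linear regression with bootstrapped intervals.

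The section also applies a one-in-ten rule to all regressions. Under Outcomes, 30-day complications are a secondary endpoint and 30-day mortality is exploratory. The recruitment section gives 50 patients, 25 per arm.

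**The concern.** Deviance and Pearson residuals are diagnostics of generalised linear models. The models listed just before the check include logistic regression, and nothing takes it out. For a 0/1 outcome these residuals are discrete and split into a positive and a negative group, so their departure from normality says nothing about whether the model fits. An analyst who follows the section would see a failed check on a sound analysis.

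What happens next is unclear. The only later sentence that mentions logistic regression offers a different link function, and it can be attached either to the binary endpoints or to the inflammatory markers. In the first case the reported effect measure could be chosen after the data are seen. In the second, a continuous concentration is handed to a model for yes/no data.

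**Working it through.** The plan gives no figure to reproduce here. The check has four steps.

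**Inputs.** 25 patients per arm (recruitment section). Event risks are not stated, so 10% to 50% per arm is assumed. The worked example of 8/25 against 5/25 events is also assumed.

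**Step 1: what the residuals are in an arm-only logistic model.** Each arm's fitted risk p equals its observed proportion. The deviance residual is √(−2 ln p) for a patient with the event and −√(−2 ln(1−p)) for one without.

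- Arm with 8/25, p = 0.32: +√(−2 ln 0.32) = 1.510 and −√(−2 ln 0.68) = −0.878.
- Arm with 5/25, p = 0.20: +√(−2 ln 0.20) = 1.794 and −√(−2 ln 0.80) = −0.668.

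Fifty patients therefore give four distinct values, with none between −0.668 and 1.510. Pearson residuals behave the same way: √((1−p)/p) with the event and −√(p/(1−p)) without.

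**Step 2: how often a correct model would look wrong.** 2,000 trials were simulated at each of the risk pairs 10/10%, 30/20%, 40/40% and 50/50%. Trials with no events or all events in an arm were dropped. A Shapiro-Wilk test at 5% stood in for the visual plot.

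| Model | Deviance residuals rejected | Pearson residuals rejected |
|---|---|---|
| Arm only | 100% | 100% |
| Arm plus one continuous covariate | 99.8–100% | 95.7–100% |

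The largest deviance-residual p-value in the arm-only runs was 0.00002. The covariate row comes from a second set of 1,000 trials per scenario, at risk pairs 50/50%, 30/20%, 20/10% and 30/30%.

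**Step 3: what another link would change.** An arm-only model has two parameters for two proportions, so it is saturated. Every link reproduces 0.32 and 0.20. Under the logit link the coefficient is ln[(5/20)/(8/17)] = ln 0.531 = −0.63, with standard error √(1/8 + 1/17 + 1/5 + 1/20) = 0.659. This gives z = −0.96 and p = 0.337.

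| Link | Deviance | Coefficient | Meaning |
|---|---|---|---|
| Logit | 56.36 | −0.63 | log odds ratio (OR 0.531) |
| Probit | 56.36 | −0.37 | no odds-ratio meaning |
| Complementary log-log | 56.36 | −0.55 | exp = 0.579, not an odds ratio |
| Cauchy | 56.36 | −0.74 | no odds-ratio meaning |
| Log | 56.36 | −0.47 | log risk ratio (RR 0.625) |

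All five give the same four deviance residuals, so the residual check fails identically after the change. Wald p-values run from 0.334 to 0.375. The likelihood-ratio p is 0.332 under every link, because the deviance with and without arm is the same. With one continuous covariate the fit is no longer identical. The larger log-likelihood change of probit and complementary log-log against logit had a median of 0.06 to 0.09 and a 95th percentile of 0.32 to 0.50, which is negligible in most trials.

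**Step 4: which model the link sentence belongs to.**

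- *Remedy for the binary endpoints.* It is the only fallback naming logistic regression, and speaking of another link makes sense only for a model already fitted as logistic. Steps 1 to 3 then apply: the trigger is met by correct models, the change gains nothing in an arm-only model, and the odds ratio is given up.
- *Fallback after the gamma mixed model.* The sentence follows that step directly, and its reference to the residuals points there. A CRP or cytokine concentration would then go to logistic regression with no cut-point stated, and the binary models would keep an invalid check with no stated response.

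**The case against.** A reader might infer that the protocol definitely moves the complication analysis to another link. The documents do not support that. Grammatically the link sentence continues the mixed-model chain, and on that reading no rule alters the link for complications and the promise of odds ratios stands. This objection holds against the stronger inference. It does not clear the sentence, because the literal reading is unworkable for continuous markers.

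The check also does not name logistic regression. It follows the Poisson/linear sentence most closely, and the one later rule that names deviance residuals is for Poisson. So its application to the logistic models rests on the list of models before it and on the absence of an exemption. That is the natural reading, but it is not spelled out.

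The 100% figure comes from a formal test, whereas the plan uses plots, and exact saturation needs an arm-only model, which the section does not specify. Both points are fair. Yet four discrete values with a wide gap will not resemble a normal sample on a plot. The one-in-ten rule also makes arm-only likely, since arm plus one covariate needs about 2 × 10 = 20 events, or 40% of 50 patients.

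Finally, the numerical consequence is small. The coefficients sit on different scales, so their spread is largely a change of units and not a change of effect. The p-values barely move, and the section also allows chi-square or Fisher tests for categorical variables. All of this stands, and it limits the point to the effect measure and the prespecification.

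**Conclusion.** The point holds in a limited form. The normality check, as placed and without exemption, is invalid for complications and 30-day mortality. The link-change sentence is defective on both available readings, although which one was intended cannot be settled from the text.

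The size is modest. In the assumed example no conclusion changes. What could be lost is a prespecified, interpretable effect measure for a secondary and an exploratory endpoint. Whether the check extends to the logistic models is inferred from the order of the text. The no-gain result is exact for an arm-only model and approximate with a covariate. The rejection rates depend on assumed risks of 10% to 50%, but the four-value structure does not. This should be corrected, but it does not threaten the trial.

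**What to change.** 1. Restrict the residual-normality check to the linear and mixed-effect models.
2. Delete the sentence that offers logistic regression with another link.
3. State that binary outcomes keep the logit link, with the odds ratio and 95% CI, whatever the residual plots show.
4. If a covariate is added to a logistic model, check fit by comparing observed with predicted risk.

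Reporting a risk difference beside the odds ratio is optional; it does not follow from this error. The change edits two sentences and adds a short statement. It needs no new data, no change of design and no change to sample size.
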